## Abstract

Despite long-standing availability of an effective vaccine, tetanus remains a significant problem in many countries. Outcome depends on access to mechanical ventilation and intensive care facilities and in settings where these are limited, mortality remains high. Administration of tetanus antitoxin by the intramuscular route is recommended treatment for tetanus, but as the tetanus toxin acts within the central nervous system, it has been suggested that intrathecal administration of antitoxin may be beneficial. Previous studies have indicated benefit, but with the exception of one small trial no blinded studies have been performed.

The objective of this study is to establish whether the addition of intrathecal tetanus antitoxin reduces the need for mechanical ventilation in patients with tetanus. Secondary objectives: to determine whether the addition of intrathecal tetanus antitoxin reduces autonomic nervous system dysfunction and length of hospital/ intensive care unit stay; whether the addition of intrathecal tetanus antitoxin in the treatment of tetanus is safe and cost-effective; to provide data to inform recommendation of human rather than equine antitoxin.

This study will enroll adult patients (≥16 years old) with tetanus admitted to the Hospital for Tropical Diseases, Ho Chi Minh City. The study is a 2x2 factorial blinded randomized controlled trial. Eligible patients will be randomized in a 1:1:1:1 manner to the four treatment arms (intrathecal treatment and human intramuscular treatment, intrathecal treatment and equine intramuscular treatment, sham procedure and human intramuscular treatment, sham procedure and equine intramuscular treatment). Primary outcome measure will be requirement for mechanical ventilation. Secondary outcome measures: duration of hospital/ intensive care unit stay, duration of mechanical ventilation, in-hospital and 240-day mortality and disability, new antibiotic prescription, incidence of ventilator associated pneumonia and autonomic nervous system dysfunction, total dose of benzodiazepines and pipecuronium, and incidence of adverse events.

**Trial registration:** ClinicalTrials.gov
NCT02999815

**Registration date: **21 December 2016

**Abbreviations:** CSF, cerebrospinal fluid; ICU, intensive care unit; IU, international units; AE, adverse event; SAE, serious adverse event; UAE, unexpected adverse event; ADL, activities of daily living; QALY, quality adjusted life year; OUCRU, Oxford University Clinical Research Unit

## Introduction

Tetanus is a vaccine-preventable disease that continues to occur despite several decades of sustained global health programs. Recently outbreaks of tetanus have been reported after natural disasters such as tsunamis and earthquakes
^1^. The true global burden of disease is unknown as reliable figures are only collected for cases of neonatal tetanus, but in 2015 the disease caused an estimated 48,199 to 80,042 deaths
^2^. Most of these deaths were in South and Southeast Asia and Sub-Saharan Africa, thus it is likely that a significant proportion of the population in these regions remains vulnerable to tetanus.

Severe tetanus, with frequent muscle spasm requires intensive care unit (ICU) treatment as patients require paralysis and mechanical ventilation to overcome muscle spasms. With good ICU management the mortality rate from tetanus can be reduced significantly, however these facilities are often unavailable in settings where most tetanus occurs
^3^. Even if they are available, patients require expensive and prolonged ICU stays with long periods of mechanical ventilation and its attending complications
^4,
5^. A recent review of outcomes in Africa highlighted the continuing high mortality rates and attributed this to the inability to access ICU facilities even if they were present
^6^.

Reducing the requirement for mechanical ventilation or shortening ICU stay should improve outcome of tetanus in all settings.

Standard tetanus treatment regimens include the administration of intramuscular tetanus antitoxin
^7^. Administration of tetanus antitoxin using the intrathecal route offers a potential benefit in treating severe tetanus as tetanus toxin acts within the central nervous system (CNS). Case series and small randomized trials have reported large ( some >50%) improvements in mortality and hospital stay in both adults and neonates treated with intrathecal antitoxin
^8–
19^. However, most reports are of poor quality with large methodological differences and possible biases. Only one blinded trial has ever been performed
^12^ recruiting a total of only 36 patients. A meta-analysis of 942 patients from randomized trials concluded the combined relative risk for mortality of intrathecal versus intramuscular antitoxin was 0.71 (95% CI 0.62–0.81)
^20^. However this meta-analysis contains some serious methodological errors and two recent reviews have concluded that there is still insufficient evidence regarding its use
^21,
22^.

Current treatment for tetanus in Vietnam consists of intramuscular equine antitoxin. One randomized controlled trial has compared equine antitoxin in the treatment of tetanus with human antitoxin (human tetanus immunoglobulin) in a total of 130 neonates. There was no difference in complications and no side effects attributable to antitoxin were apparent in either group
^23^. Currently in Vietnam, human antitoxin is more expensive and is only just becoming available, although it is the product recommended by the World Health Organization due to a theoretical improved side-effect profile (with a reduced risk of serum sickness and anaphylactic reactions)
^7,
24^. Better understanding of the side-effect profile and use of human versus equine preparations would be useful in Vietnam and many low and middle income countries when choosing which preparation to use. 

The primary aim of this study is to assess the benefit of additional intrathecal tetanus antitoxin to intramuscular regimens. However, due to the factorial design of this study, we are also able to compare the side effect profile of equine and human antitoxin.

## Protocol

This protocol has been written according to the SPIRIT guidelines, see
Supplementary File 1 and
Supplementary File 2.
Figure 1 shows the study flowchart.

**Figure 1. f1:**
[figure not shown]
Study flowchart.

### 1 Objectives

***1.1 Primary objective.*** To establish whether the addition of intrathecal tetanus antitoxin reduces the need for mechanical ventilation in patients with tetanus.

***1.2 Secondary objectives***

•To determine whether the addition or intrathecal tetanus antitoxin reduces autonomic nervous system dysfunction and length of hospital/ICU stay.•To establish whether the addition of intrathecal tetanus antitoxin in the form of Tetagam-P is safe and cost-effective.•To provide data to inform the recommendation of human rather than equine antitoxin

### 2 Study design

We will conduct a randomised partially-blinded controlled 2#215;2 factorial trial. First, adults admitted to the ICU at the Hospital for Tropical Diseases will be randomized to receive either human (3000 IU) or equine (21,000 units) intramuscular antitoxin. Second, participants will be randomized to receive either standard treatment with intramuscular antitoxin alone or with the addition of 500 IU intrathecal human antitoxin. Patients with contra-indications to lumbar puncture or antitoxin treatment will be excluded. Patients who have already received a treatment dose of intramuscular antitoxin will have the intramuscular injection omitted.

All patients will receive other standard tetanus treatment as deemed necessary by the attending physicians. Spasms will be treated with benzodiazepines as first-line therapy. Patients with spasms not controlled with benzodiazepines will receive tracheostomy, paralysis, magnesium sulphate and mechanical ventilation. Heart rate, blood pressure, respiratory rate, temperature, oxygen saturation and daily drug use will be recorded throughout the ICU stay. Patients will be followed following discharge from hospital until 240 days for disability/ death.

***2.1 Primary end point***

•Requirement for mechanical ventilation during ICU stay

Criteria for mechanical ventilation are SpO
_2_ <90%; or PaO
_2_/F
_i_0
_2_ <250; or excessive spasms necessitating muscle paralysis. 

These criteria are intended as a guide and the final decision to ventilate a patient rests with the individual doctor responsible for the patient.

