### 5 Statistics

***5.1 Sample size justification.*** Data from the Hospital for Tropical Diseases in 2013 showed that 40% of patients with tetanus required ventilation (43 out of 110 in a 6 month period). However an estimated 4–6% of patients did not have generalized tetanus and would be excluded from study entry. Therefore we estimate that 45% of study subjects without intrathecal treatment will require mechanical ventilation in our study. The main comparison of this 2x2 factorial trial is the comparison between subjects receiving intrathecal human antitoxin versus those without intrathecal treatment. To detect an absolute risk reduction for mechanical ventilation due to intrathecal treatment by 17% (from 45% to 28%) with 80% power at the two-sided 5% significance level, 250 subjects are required. To account for some protocol violations and losses to follow-up, the trial will randomize a total of 272 patients (68 in each of the four treatment arms in the 2x2 factorial trial). Should the ventilation rate in the control arm be lower than anticipated, this samples size will also detect a reduction from 40% to 24% with 80% power.

Regarding the secondary endpoint of ICU stay, median (interquartile-range) duration of ICU stay from historic data of 111 tetanus admitted to the Hospital for Tropical Diseases was 13
^4–
22^ days. Based on simulation and these historical data, 272 subjects will provide 88% power to detect a relative reduction in the ICU stay by 25% using the Cox proportional hazards model.

***5.2 Description of statistical methods.*** The primary analysis population for all analysis is the full analysis population containing all randomized patients. Patients will be analyzed according to their randomized arm (intention-to-treat). Analyses for the primary endpoint will be repeated on the per protocol population which excludes the following patients: patients not receiving the randomized intervention and other major violations of inclusion/exclusion criteria or study procedures. 

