The primary outcome measure, requirement for mechanical ventilation during ICU stay, will be summarized as x/n (%) in each group and compared between the groups based on a logistic regression model with the two interventions (intrathecal treatment vs. sham procedure, human vs equine intramuscular treatment) as the only covariates without an interaction term. The main comparison is the comparison between intrathecal treatment vs. sham procedure, but the effect of the second randomized intervention will also be summarized as a secondary comparison. As odds ratios from logistic regression are somewhat difficult to interpret for a clinical audience, we will additionally summarize relative risk reductions between the groups based on a binary regression model with a log-link rather than the logit link function used in logistic regression. Interactions between the two interventions are not expected and interaction tests will have low power but we will nevertheless assess potential interactions informally through interaction plots and formally through a likelihood ratio test for an interaction in the logistic regression model. Should the interaction test reach formal significance, we will also perform pair-wise comparisons between the 4 treatment arms.

Potential heterogeneity of the treatment effect will be assessed based on appropriate interaction (likelihood ratio) tests and the following pre-defined sub-grouping variables:

•The Tetanus Severity Score
^27^ (calculated based on information available prior to randomization only) stratified according to tertiles of the observed TSS.•Age: (≤70, 71-80, >80 years)•Pre-existing medical conditions: moderate severe illness, severe illness defined according to ASA physical state scale•Anti-toxin prior to admission

In addition, the primary endpoint will be modelled using a logistic regression model including the two interventions plus additional adjustment for the Tetanus Severity Score, age and pre-existing medical conditions.

Duration of hospital stay, duration of ICU stay, and 240 day mortality will be visualized using Kaplan-Meier curves for all 4 study arms and, additionally, for all patients with and without intrathecal treatment. Formal comparisons of these outcomes (and in-hospital mortality) will be based on Cox regression models with the two interventions as the only covariates using a similar analysis strategy as for the primary outcome described above. 

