The intrathecal intervention group will have the additional risk of lumbar puncture. The most serious complication that may be linked to lumbar puncture is cerebral herniation. This has never been reported in patients treated with intrathecal antitoxin in tetanus. This event is argued to be a result of associated raised intracranial pressure not the lumbar puncture procedure and as raised intracranial pressure does not occur in tetanus the risk of this event is extremely low (<0.001%). No lumbar punctures will be performed if the patient is suspected of having raised intracranial pressure or has a contra-indication to lumbar puncture. Other risks of lumbar puncture include infection (rare and currently < 0.1% at Hospital for Tropical Diseases), headache and venous puncture. Staff who will be performing the lumbar puncture are highly experienced clinicians who have performed this procedure >500 times.

Risks of intrathecal antitoxin use

Studies using intrathecal antitoxin report a low incidence of AEs. Most older studies used either equine antitoxin or human antitoxin preparations containing thimerosal preservative, which has been suggested to be responsible for many of the side effects. Only 1 published study of human tetanus immunoglobulin has reported the exact formulation used. In this study by Menon
*et al.*, 41 patients were treated with TetGlob, a product containing thimerosal. One patient was reported to have mild learning difficulties and cerebral palsy on long-term follow up; a child aged of 11 months at the time of treatment, the authors felt this was most likely due to the age of the child and severity of disease. Studies in Africa have reported incidence of learning difficulties and cerebral palsy to be 20–40% in survivors of neonatal tetanus
^28,
29^ treated without intrathecal antitoxin.

Tetagam-P used in this study contains no preservatives or alcohol.

In clinical trials involving 947 patients treated with intrathecal antitoxin there were 3 cases of neonatal death. These consist of 2 cases of ‘apnea’ in Chugh
*et al.’s* study in 1984 and 1 case of sudden death 1 hour after intrathecal injection of 250 units equine antitoxin/ and 6 ml hydrocortisone in a neonate. Unfortunately the paper by Chugh

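### A death in ICU without ventilation is scored like recovery without ventilation on the primary endpoint, and no listed analysis of that endpoint treats it as a failure

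*Protocol article*

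**What the plan says.** Section 2.1 of the protocol article defines the primary endpoint as "Requirement for mechanical ventilation during ICU stay". It lists oxygenation and spasm criteria but presents them as guidance, adding that "the final decision to ventilate a patient rests with the individual doctor responsible for the patient".

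Section 5.2 fixes the denominator: "The primary analysis population for all analysis is the full analysis population containing all randomized patients". It also fixes the summary and the model: the outcome "will be summarized as x/n (%) in each group and compared between the groups based on a logistic regression model", with the two randomized interventions as the only covariates. The other listed analyses of this endpoint are a log-link model for relative risk, an interaction test, four subgroup analyses, a covariate-adjusted logistic model and a per-protocol repeat. All keep the same yes/no ventilation outcome.

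Death is handled elsewhere. In-hospital and 240-day mortality are secondary endpoints (section 2.2) compared by Cox regression (section 5.2). Deaths are also reported to the ethics committee (section 4.4), and the monitoring board reviews unblinded safety data (section 4.5). The Discussion says that mortality in the unit is low. No rate is given, either for death overall or for death without ventilation.

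**The concern.** Death before ventilation makes the endpoint event impossible. With a plain yes/no outcome over everyone randomized, that patient becomes a non-event, which is the favourable category. The endpoint definition itself produces this scoring, so it is not only a matter of analysis detail.

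At stake is how a reduction in ventilation can be read. If one arm has more unventilated deaths, and some of those patients would have gone on to ventilation, part of that arm's lower rate reflects death and not milder disease. A reader of the primary result alone could not separate the two. Total in-hospital mortality does not separate them either, because it mixes deaths after ventilation with deaths without it.

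**Working it through.** **Inputs from the protocol (section 5.1).** 45% versus 28% ventilated; two-sided 5%; 80% power; 250 required; 272 randomized as 68 per arm, so 136 versus 136 for the intrathecal comparison.

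**Reproducing the stated size.** The protocol states "with 80% power at the two-sided 5% significance level, 250 subjects are required". With p̄ = (0.45+0.28)/2 = 0.365,

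n per group = [1.96·√(2·0.365·0.635) + 0.8416·√(0.45·0.55+0.28·0.72)]² / 0.17² = 124.7, rounded up to 125, so 250 in total.

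Allowing 8% loss, 250/0.92 = 271.7, which gives 272. The stated figures reproduce.

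**Near the boundary.** For equal groups of 136, the uncorrected chi-square for a versus b events is χ² = (a−b)²·272 / [(a+b)(272−a−b)]. This approximates the planned logistic comparison. The event counts and numbers of deaths are illustrative assumptions, because the document gives none. The composite adds unventilated deaths to the ventilated count.

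| Scenario | Control vs intrathecal | χ² | p |
|---|---|---|---|
| Ventilation only | 54 vs 38 | 4.205 | 0.040 |
| One intrathecal death counted as failure | 54 vs 39 | 3.676 | 0.055 |
| Three intrathecal deaths counted | 54 vs 41 | 2.734 | 0.098 |
| Three deaths in each arm counted | 57 vs 41 | 4.084 | 0.043 |
| Design effect, ventilation only | 61 vs 38 | 8.401 | 0.0037 |
| Design effect, three intrathecal deaths counted | 61 vs 41 | 6.275 | 0.012 |

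One-sided deaths can change a borderline result. Balanced deaths barely move it, and at the full design effect three one-sided deaths leave it significant.

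**Under no true effect.** Assume 45% would need ventilation in both groups and d extra unventilated deaths occur in the intrathecal group. If a fraction f of them would otherwise have been ventilated, the intrathecal rate is 0.45 − f·d/136. The chance of a significant result favouring intrathecal treatment, nominally 2.5%, becomes:

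| d | f = 1 (rate; chance) | f = 0.45 (rate; chance) |
|---|---|---|
| 2 | 43.5%; 4.3% | 44.3%; 3.2% |
| 5 | 41.3%; 8.9% | 43.3%; 4.6% |
| 10 | 37.6%; 23.2% | 41.7%; 7.9% |

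With f = 0 the rate and the error chance do not move. The deaths are then invisible in the endpoint but do not bias it. On the composite, the intrathecal rate stays at 45% when f = 1. When f = 0.45 it rises to 45.8%, 47.0% or 49.0%, so the harm shows in the right direction.

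**Cost in power.** If unventilated death adds 1%, 2%, 3% or 5% to both groups (an assumption) and the 17-point difference is kept, 80% power needs 254, 256, 258 or 262 patients. Power with 272 is 82.9%, 82.5%, 82.2% or 81.6%. The planned size covers the composite.

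**The case against.** **The remedy is SAP content.** Supportive analyses and the handling of death are often left to the SAP, which is not shown and may contain such a rule. That is fair as to the remedy. The scoring itself follows from the endpoint definition and denominator, which the protocol fixes. Reading 'requirement' as 'met the criteria' does not settle it, because the criteria are only a guide, and a sudden death may come before any criterion is recorded.

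**The protocol's own safety review.** A reader might infer that an early death caused by the intrathecal injection is a documented risk here and would count in the treatment's favour. Section 8.3 does mention "1 case of sudden death 1 hour after intrathecal injection of 250 units equine antitoxin" and two apnoea deaths. But all three deaths, among 947 trial patients, were neonatal. The sudden death followed equine antitoxin given with hydrocortisone, and the product in the apnoea cases is unknown. The same section reports no serious side effects in 390 mainly adult patients where they were specifically sought. This trial enrols patients aged 16 and over and gives preservative-free human antitoxin intrathecally. The neonatal deaths therefore do not predict its risk. Even at that crude rate, 3/947 × 136 is about 0.4 deaths. A patient with apnoea in an ICU with ventilators would also usually be ventilated, and so counted as an event.

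**Direction.** Such a death lowers an arm's rate only if that patient would otherwise have been ventilated. At the planning rates of 45% and 28%, most patients would not have been. This stands and limits the claim.

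**Visibility.** Mortality endpoints, prompt reporting of deaths and unblinded board review would show an excess of deaths. This also stands: harm would not go unseen. But these do not change the primary comparison, and a non-significant mortality result would reassure little. With 5% versus 10% mortality (an assumption), power at 136 per group is only about 35%.

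**Conclusion.** The point holds in a limited form. As written, the primary endpoint does not distinguish death without ventilation from recovery without ventilation, and no listed primary-endpoint analysis does so either. An imbalance would favour the arm with more such deaths, to the extent that those patients would otherwise have been ventilated. In the remaining cases the death is simply recorded as a good outcome.

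The effect is probably small. It could decide the conclusion only if the result is close to the 5% boundary and the deaths fall mainly in one arm. The number of such deaths is assumed throughout. The documents do not support the stronger reading that intrathecal treatment is expected to cause such deaths, or that every such death would improve its result.

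**What to change.** Keep the primary endpoint and the sample size. Add to section 5.2 a pre-specified sensitivity analysis of 'mechanical ventilation or death in ICU', using the same logistic and log-link models and the same population. Report the number of deaths without ventilation by arm beside the primary result. If the two analyses disagree, any statement of benefit should say so.

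The cost is one extra analysis on data already collected and a sentence or two of text. It should be fixed before unblinding so that it cannot appear chosen in the light of the results.

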***2.2 Secondary End Points***

•Duration of ICU stay•Duration of hospital stay•Duration of mechanical ventilation•In hospital and 240-day mortality and disability•New antibiotic prescription during ICU stay (excluding antibiotics for tetanus or initial entry site infection)•Incidence of Ventilator Associated Pneumonia•Incidence of the clinical syndrome of autonomic nervous system dysfunction•Total dose of benzodiazepines and pipecuronium during hospital stay•Incidence of adverse events

